### **7. Number of missing values/incomplete cases**

Assessed by data management team, based on data in Prospect database.

### **8. Participant/interventionist and members of MDT views on research protocols**

Assessed through qualitative interviews and to include:

- Barriers to recruitment, problems encountered in reaching participants [38];
- Perceived problems with trial procedures such as recruitment, informed consent etc.
- Acceptability
- Perceived utility and burden of outcome assessments.

### **9. A survey on the content of usual care at participating centres**

A CTRU staff member will complete this survey with the principal investigator, a senior medic or delegate working at the participating centre.

## **7.3 Process data relating to the implementation of the intervention**

### **1. Context**

Definitions of ‘context’ tend to cluster around setting, roles, interactions and relationships [39]. It is important that context is understood as diachronic and emergent rather than synchronic and static [40, 41]. Frameworks for process evaluation have defined ‘context’ as:

- “aspects of the larger social, political, and economic environment that may influence intervention implementation” [42];
- “factors external to the intervention which may influence its implementation, or whether its mechanisms of impact act as intended” [43].

The context, and its interaction with implementation, mechanisms of impact, outcomes, the description of the intervention and its causal assumptions [43] will be described using qualitative data from research interviews, field notes, study management logs, minutes and e-mails. The focus will be how the context of individual CF Units affects implementation of the intervention and its potential outcomes.

### **2. Implementation**

Definitions of ‘implementation’ tend to cluster around the processes or stages of adoption, the methods, means or social organisation of bringing innovative practices into use [39]. One way of describing the process of getting research into practice is to use a process model [44]. To structure our narrative of how the complex intervention was implemented we will use a process model called the Quality of Implementation Framework [45].

### **3. Recruitment:**

Based on e-mails and minutes we will describe in narrative terms, the procedures used to approach and attract to the project NHS Trusts and interventionists [42].

#### **4. Training:**

The comprehensiveness of the training component of the intervention for the health professionals delivering the intervention will be assessed by a combination of audio recordings of consultations and by interview.

#### **5. Fidelity**

“The extent to which the intervention was delivered as planned. It represents the quality and integrity of the intervention as conceived by the developers. Fidelity is a function of the intervention providers.”[42]

- Interaction with participant along lines recommended by manual, determined by audio recordings of consultations between the interventionist and PwCF in the intervention arm.
- Recommendation of appropriate CFHealthHub tasks by interventionist, determined by audio recordings and by data from CFHealthHub;

The fidelity assessment will be developed and based on a tool used by Borelli et al [46].

#### **6. Use [38] / dose received [42] of intervention**

Use of CFHealthHub by participant, as proposed by interventionist, determined by data capture by CFHealthHub, including the online activities started and completed, minutes spent on recommended pages and which parts the participant has picked out and put in a “my favourites” page. The number of times, frequency over time and duration with which users log on to CFHealthHub, as well as the activities they perform while logged in, described quantitatively using data from CFHealthHub.

A record of the discussion between the interventionist and the MDT will be kept. This will include who was there, brief notes of what was discussed and any agreement of treatment goals made.

#### **7. Acceptability**

The acceptability of the intervention to hospital staff and PWCF assessed through semi-structured interviews.

#### **8. Perceived benefits and harms**

Assessed through semi-structured interviews with health professionals and PWCF.

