### 10.2.4 Undertaking the interviews

For the interviews we have developed topic guides based on our research questions and these are attached to the application. Topic guides develop throughout any qualitative interview study and our topic guides may change as the study progresses. We will audio record all interviews after receiving written permission to do so. We will use an encrypted digital recorder. Reflexive notes will be made during and after the interviews. We expect

interviews to last around one hour. We do not expect data saturation in pilot studies; the aim is to identify any learning that can be addressed in preparation for the full trial.

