**Now I'd like to ask you about your meetings with the person who has been working with you on CFHealthHub.**

3. What types of things did they recommend that you do? [prompts: setting goals, solving problems, making plans (myplan), giving you information]
4. Do you think you have had any benefit from these meetings?  
  
**If yes**, what benefit and what about the service helped you to get this?  
  
**If no**, what has stopped you gaining benefit?
5. What was good about how the meetings were delivered? [Prompt: what needs to be improved?]

Pilot – ACtiF Intervention Patient Topic guide: v1 2Feb16

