**Now I'd like to talk to you about the CFHealthHub website / app.**

6. What was good about the website? [Prompts: my plan, how am I doing, tool kit, graphs, my treatment]
7. What needs to be improved? [Prompts: my plan, how am I doing, tool kit, graphs, my treatment]
8. Do you think you've had any benefit from using the website?  
**If yes**, what benefit and what about the website helped you to get this?  
**If no**, what has stopped you gaining benefit?
9. Have the website and/or meetings helped you to improve how often you use your nebuliser?  
**If yes**, how has it helped you to do this?  
**If not**, why not?
10. How do the CFHealthHub website and the meetings work together?
11. Has using CFHealthHub helped you to be able to use your nebuliser any better? Why / Why not? [Prompt: capability skills / knowledge including beliefs]
12. Has using CFHealthHub helped you to find the time to use your nebuliser more? Why / why not? [Prompt: opportunity / making plans]
13. Has using CFHealthHub made you want to use your nebuliser more? Why / why not? [Prompt: motivation and confidence]
14. How does the CFHealthHub service (website and meetings) fit with the care you were already receiving at the unit/hospital?

15. Do you think you would continue using CFHealthHub? [Prompt: during the study / after the study]
16. Is CFHealthHub a good thing to use in general for people with CF? Why? / Why not?
17. How have you found being part of the study?

Is there anything else that we haven't talked about that you'd like to comment on?

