**General questions:**

- 10. How engaged did participants seem with CFHH? [Prompt: What feedback if any have you had from participants about CFHH?]
- 11. How useful do you think CFHH is for your participants?

12. How easy / difficult has it been to get your participants to use CFHH?
13. Have you seen any changes to the ways in which your participants use their nebulisers since starting CFHH?
14. What have you learnt from using CFHH with your participants?
15. What if any are the benefits to you and / or to your participants of using CFHH?
16. How do you think CFHH fits with the other care offered by the centre?
17. How have you found being part of the trial?

Is there anything else you'd like to say about CFHH?

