### **ACTiF Pilot Study**

### **MDT Topic guide**

*Thank you for agreeing to take part in the interview today.*

*Check timing ok*

*Check consent form filled in / received*

*Are you happy for the interview to be recorded?*

*We're interested in your views of the CFHealthHub service and how it fits into the care provided in your centre.*

1. Can you describe the key things you did in your centre to help patients adhere to their nebulisers prior to the ACTiF study?
2. How does nebuliser adherence fit with the other things you do for CF patients?
3. What involvement have you had in the CFHealthHub intervention? [Prompts: website, interventionist, training of staff]
4. You had training to help you be more aware of patient activation. What did you think of the training? [Prompts: Do you think it has changed your practice in any way? If yes what changes, if no why not? Key aspects – patient knowledge including beliefs / skills / confidence]
5. Do you think CFHealthHub is a useful intervention? Why? / Why not? [Prompts: what do you think about the: website, feedback about adherence data, interventionist, training?]
6. How do you think the CFHealthHub intervention is operating in practice? [Prompt: what are the strengths / improvements needed?]
7. How does the CFHealthHub intervention fit with the care offered by your centre?
8. How does the CFHealthHub intervention help your patients to know how to use their nebuliser? [Prompts: Skills / knowledge / beliefs. How / Why doesn't it help?]
9. How does the CFHealthHub intervention help your patients to find ways to use their nebuliser more? [Prompts: How / Why doesn't it help?]

Pilot – ACTiF MDT Topic guide v1 2Feb16

10. How does the CFHealthHub intervention help to motivate your patients to use their nebuliser?  
[Prompts: How / Why doesn't it help?]

11. Do you think CFHealthHub is helping your intervention patients to improve their adherence? If yes, what key things have helped this? If no, what if anything could be done to help this?

12. Has the CFHealthHub intervention changed anything about the way in which you and/or your team approach adherence in your centre?

i) for patients receiving the intervention?

ii) for patients not receiving the intervention?

[Prompts: MDT discussions / differences between control and intervention patients]

13. Which patient groups are most likely to benefit from CFHealthHub? Why?

14. Which patient groups are least likely to benefit from CFHealthHub? Why?

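### Perceived harms are a named interview outcome, but the intervention-arm, interventionist and MDT topic guides ask directly about benefit five times and about harm never

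*Protocol*

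**What the plan says.** Protocol section 7.3 (process data on implementing the intervention) lists perceived benefits and harms as item 8. One method is given: "Assessed through semi-structured interviews with health professionals and PWCF". Section 10.2.4 states: "For the interviews we have developed topic guides based on our research questions". It adds that the guides may evolve during the study.

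Four guides are appended. In those for people who receive, deliver or work alongside the intervention, the questions that name benefit are:

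- Intervention Patient guide, Q4: "Do you think you have had any benefit from these meetings"
- Intervention Patient guide, Q8: "Do you think you've had any benefit from using the website"
- Interventionist guide, Q15: "What if any are the benefits to you and / or to your participants of using CFHH"
- MDT guide, Q13: "Which patient groups are most likely to benefit from CFHealthHub? Why"
- MDT guide, Q14: the mirror question, on the groups least likely to benefit.

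In Q4 and Q8 of the Intervention Patient guide, a no leads to "what has stopped you gaining benefit".

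**The concern.** Half of a named outcome has no direct question. On the benefit side, the interviewer is told to ask and, after a yes, to follow up. On the harm side nothing is prompted, and the lowest point the questions reach is absence of benefit.

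Unwanted effects are plausible from the protocol's own description. Participants see their objectively recorded adherence, agree a percentage goal (section 6.4.4.2) and receive colour-coded feedback against it (section 6.4.4.3). The review visit has a path for a missed goal and tells the interventionist to frame it as learning and not failure (section 6.4.4.4), so discouragement appears to have been foreseen.

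Section 11.2 uses the interviews to refine the intervention and its implementation for the full trial. Section 11.1 lists the intervention's safety among the inputs to judging whether that trial is feasible. If benefits are asked for and harms are left to be volunteered, refinement starts from an unbalanced account.

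**Working it through.** No formula applies. The check is to read every numbered question and prompt in the appended guides and count two things: questions that name benefit, and questions or prompts that name harm, distress or another unwanted effect of the intervention.

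| Guide | Numbered questions | Name benefit | Name harm or unwanted effect |
|---|---|---|---|
| Intervention Patient | 17 | 2 (Q4, Q8) | 0 |
| Interventionist | 17 | 1 (Q15) | 0 |
| MDT | 18 | 2 (Q13, Q14) | 0 |
| Total for these three | 17 + 17 + 18 = 52 | 2 + 1 + 2 = 5 | 0 |
| Control Patient (for completeness) | 11 | 0 | 0 |

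MDT Q14 is counted as naming benefit because it does so, although it asks where benefit is lacking. Without it the contrast is 4 to 0.

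Interviews run from these three guides (section 1): 20 to 24 with intervention participants, 8 with interventionists and 8 with MDT members. That is 20 + 8 + 8 = 36 to 24 + 8 + 8 = 40.

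Other planned routes by which harm could surface:

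- **Critical or open questions.** The Intervention Patient guide asks "What needs to be improved" (Q7), whether CFHealthHub is good for people with CF and why or why not (Q16), and how the study was found (Q17). The Interventionist guide asks what could be improved at each step, what feedback participants gave (Q10) and whether nebuliser use changed (Q13). The MDT guide asks why the intervention is or is not useful (Q5) and what needs improving (Q6). All guides close with an open question. These invite criticism, but none asks whether anything had a bad effect.
- **Drop-out interviews.** Section 10.2.2 plans 2 to 3 with people who leave the intervention, to learn why. They could reveal harm, but not among people who were upset and stayed.
- **Questionnaires.** PHQ-8 and GAD-7 are taken at consent and at about 5 months in both arms (Table 3). They measure mood, not what a person attributes to the intervention.
- **Adverse event reporting.** Section 12.3 covers events reported by sites, including newly diagnosed depression that requires treatment. It does not collect perceived harm by interview.

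Each route supplies something near item 8. None supplies a prompt for its harm half.

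**The case against.** The strongest reply is that these are semi-structured interviews, not fixed questionnaires. A competent interviewer follows leads, the guides may change, every guide ends openly, and people who leave are asked why. Distress and low mood are measured separately by PHQ-8 and GAD-7, staff enquire about adverse events at clinic appointments (section 12.3.4), and concerns arising during the work go to the clinical team (section 6.4.4). On this view the missing question is a matter of wording.

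Much of that stands, and it limits the point. A reader might infer several stronger things that the protocol does not support:

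- **That the guides ask only about benefit.** They do not: improvements, usefulness, reasons against and experience of the study are all covered.
- **That the interviews will yield almost no harms.** That is a prediction. Harms can come up through the open questions, the drop-out interviews or later changes to the guides.
- **That burden is ignored altogether.** Both patient guides prompt on the volume of paperwork, although this is burden of the research, not of the intervention.
- **That the choice of secondary measures will be distorted.** Section 11.2 links that choice to perceived benefits only, so harms were never a stated input. The use at risk is refinement of the intervention.
- **That the Control Patient guide shares the fault.** Item 8 concerns implementation of an intervention that controls do not receive. Section 10.2.2 gives their interviews a different purpose: patient activation and leakage.

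The reply does not remove the asymmetry. Freedom to follow a lead helps only once the interviewee raises it, and permission to change a guide is not a commitment to add a harm question.

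**Conclusion.** The mismatch holds. Section 7.3 item 8 promises perceived harms from interviews, and the three relevant guides contain five questions naming benefit and none naming harm. The reasonable conclusion is that perceived harms are likely to be under-collected relative to benefits. By how much cannot be derived from the protocol.

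This rests on two assumptions: that interviewers broadly follow the guides as appended, and that direct questions elicit more than open ones. It does not affect the recruitment or retention criteria, the quantitative outcomes or formal safety reporting. It should be corrected because it leaves part of a stated outcome poorly measured and is easily repaired.

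**What to change.** Add one neutral question, with matching wording, beside the benefit question in three guides:

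- **Intervention Patient guide:** has anything about the meetings, the website or seeing your own data been unhelpful or upsetting, or made things worse? If so, what?
- **Interventionist and MDT guides:** have you seen any unhelpful or unwanted effects of the intervention on patients? If so, what?

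In the patient guide, ask it whatever the answer on benefit, so that it does not depend on a no. State under section 7.3 item 8 that benefits and harms will be reported side by side. Leave the Control Patient guide as it is.

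The cost is an amendment to three guides and slightly longer interviews, with none added. Section 13.2 allows for substantial and minor amendments; which applies is for the sponsor to decide. Deleting harms from item 8 would also restore consistency, but would give up information the study says it wants.

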#### **9. Leakage of intervention to controls**

Assessed through audio recordings of consultations between the MDT, interventionist, and PwCF in the control arm, and semi-structured interviews with PwCF in the control arm.

### **7.4 Clinical outcomes and covariates**

The time schedule of enrolment, interventions (including any run-ins and washouts), assessments, and visits for participants can be found in Table 3 and Table 4 below.

#### **7.4.1 Primary clinical outcome**

The primary clinical outcome is the number of pulmonary exacerbations in 5 (+/-1) month post-baseline follow-up period, defined according to the Fuchs criteria [47]. An exacerbation of respiratory symptoms will be said to have occurred when a patient was treated with parenteral antibiotics for **any one of the following 12 signs or symptoms** [48]:

1. change in sputum;
2. new or increased hemoptysis;
3. increased cough;
4. increased dyspnea;
5. malaise, fatigue, or lethargy;

6. temperature above 38 °C;
7. anorexia or weight loss;
8. sinus pain or tenderness;
9. change in sinus discharge.
10. change in physical examination of the chest, derived from notes by site staff.
11. decrease in pulmonary function by 10 percent or more from a previously recorded value, derived from notes by site staff; or,
12. radiographic changes indicative of pulmonary infection, derived from notes by site staff.

The trial interventionist or prescribing clinician/nurse will collect data on the “exacerbations” form at the point of a participant starting a course of IV antibiotics.

#### 7.4.2 Secondary clinical outcomes

##### 1. Body Mass Index (BMI).

2. **Forced expiratory volume in 1 second (FEV1):** standardised spirometry as a measure of condition severity [49].

3. **EuroQol EQ-5D-5L:** generic health status measure for health economic analysis [50].

4. **The Patient Activation Measure (PAM-13) (Health Style Assessment):** assessment of patient knowledge, skill, and confidence for self-management [51]. \*PAM-13 was labelled as “Health Style Assessment” following a request from the licence owners to ensure the purpose of the questionnaire is clear for participants.

5. **Assessment of routine :** measure of life chaos [52].

6. **Self-Report Behavioural Automaticity Index (SRBAI):** automaticity-specific subscale of the Self Report Habit index to capture habit-based behaviour patterns [53].

7. **Cystic Fibrosis Questionnaire-Revised (CFQ-R):** disease specific health-related quality of life instrument [54].

8. **The Patient Health Questionnaire depression scale (PHQ-8):** severity measure for depressive disorders [55].

9. **MAD (Medication Adherence Data-3 items) :** medication adherence measure

10. **The General Anxiety Disorder 7-item anxiety scale (GAD-7):** severity measure for anxiety [56].

11. **The Capability Opportunity Motivation Behaviour Beliefs Questionnaire (COM-BMQ):** This questionnaire incorporates:

- a. **The Beliefs about Medicines Questionnaire - specific (Nebuliser adherence) (BMQ 21-item):** a validated self-report tool[57], customised by the author to identify perceived necessities and concerns for nebuliser treatment.
- b. The following project-specific items: one additional belief item, one intention item, one confidence item, and a list of barriers. These will serve as a tailoring tool for the intervention and also as a secondary outcome measure.

12. **Subjective adherence single question:** self-report estimate of adherence as a percentage. Self-reported problems: identification of capability and opportunity barriers to nebuliser adherence

13. **Concomitant medications:** bespoke instrument, designed for this research project.
14. **Resource use form:** interventionist collects data from a combination of hospital notes and the NHS patient electronic system to determine 1) inpatient IV days 2) Routine clinic visits 3) Unscheduled outpatient contacts 3) unscheduled inpatient stays.
15. **Exploratory analysis of habit formation:** analyses with the objective nebuliser data will be performed to explore the process of habit formation with the delivery of the adherence intervention
16. **Prescription:** a monthly prescription check to both check for data transfer to CFHealthHub and review for an indication that the prescription has changed or indication of microorganism e.g. pseudomonas (please see table 2 and 3 and refer to section 10.1.1).
17. **Adherence to prescribed medication (see 7.4.3)**
18. **Any treatment with IV antibiotics**

### 7.4.3 Adherence to prescribed medication

Adherence to prescribed medication will be defined in several ways including:

1. Unadjusted adherence
2. Simple normative adherence (without numerator adjustment)
3. Sophisticated normative adherence (without numerator adjustment)
4. Simple normative adherence (with numerator adjustment)
5. Sophisticated normative adherence (with numerator adjustment)

Further detail about the outcomes will be reported in the trial statistical analysis plan.

**Table 3. Individual-level data derived from PWCF and sites**

|                                                                                                                                                                                                                                                                                                                                                                                                               | Where?   | Completed by? | Consent visit | Baseline (intervention) visit | At clinic visits | Exacerbations episode | 5 months (+/- 1 month) from consent visit | Up to 30 th April 2017 |
|---------------------------------------------------------------------------------------------------------------------------------------------------------------------------------------------------------------------------------------------------------------------------------------------------------------------------------------------------------------------------------------------------------------|----------|---------------|---------------|-------------------------------|------------------|-----------------------|-------------------------------------------|-----------------------------------|
| Enrolment                                                                                                                                                                                                                                                                                                                                                                                              |          |               |               |                               |                  |                       |                                           |                                   |
| Pre-screening form (before 1 st visit)                                                                                                                                                                                                                                                                                                                                                             | Prospect | Site          | -             | -                             | -                | -                     | -                                         | -                                 |
| Confirmation of eligibility form                                                                                                                                                                                                                                                                                                                                                                              | Prospect | Site          | ●             | -                             | -                | -                     | -                                         | -                                 |
| Informed consent                                                                                                                                                                                                                                                                                                                                                                                              | Prospect | Site          | ●             | -                             | -                | -                     | -                                         | -                                 |
| Intravenous days in last registry year                                                                                                                                                                                                                                                                                                                                                                        | Prospect | Site          | ●             | -                             | -                | -                     | -                                         | -                                 |
| Pseudomonas status +                                                                                                                                                                                                                                                                                                                                                                                          | Prospect | Site          | ●             | -                             | -                | -                     | -                                         | -                                 |
| Primary outcome                                                                                                                                                                                                                                                                                                                                                                                        |          |               |               |                               |                  |                       |                                           |                                   |
| Exacerbations form including:
Parenteral antibiotics
Change in sputum*
New or increased hemoptysis*
Increased cough*
Increased dyspnea*
Malaise, fatigue, or lethargy*
Temperature above 38 °C*
Anorexia or weight loss*
Sinus pain or tenderness*
Change: sinus discharge*
Change: phys. exam. chest*
Decrease: pulmonary function *
Indicative radiographic changes* | Prospect | Site          | ●             | -                             | -                | ●                     | ●                                         | ●                                 |
| Secondary outcomes                                                                                                                                                                                                                                                                                                                                                                                     |          |               |               |                               |                  |                       |                                           |                                   |
| BMI (height and weight)                                                                                                                                                                                                                                                                                                                                                                                       | Prospect | Site          | ●             | -                             | -                | -                     | ●                                         | -                                 |
| FEV 1                                                                                                                                                                                                                                                                                                                                                                                              | Prospect | Site          | ●             | -                             | ●                | -                     | ●                                         | ●                                 |
| EQ-5D-5L**                                                                                                                                                                                                                                                                                                                                                                                                    | Prospect | PWCF          | ●             | -                             | -                | ●                     | ●                                         | -                                 |
| PAM-13(Health Style Assessment)                                                                                                                                                                                                                                                                                                                                                                               | Prospect | PWCF          | ●             | -                             | -                | -                     | ●                                         | -                                 |
| Assessment of Routine                                                                                                                                                                                                                                                                                                                                                                                         | Prospect | PWCF          | ●             | -                             | -                | -                     | ●                                         | -                                 |
| SRBAI                                                                                                                                                                                                                                                                                                                                                                                                         | Prospect | PWCF          | ●             | -                             | -                | -                     | ●                                         | -                                 |
| CFQ-R                                                                                                                                                                                                                                                                                                                                                                                                         | Prospect | PWCF          | ●             | -                             | -                | -                     | ●                                         | -                                 |
| PHQ-8                                                                                                                                                                                                                                                                                                                                                                                                         | Prospect | PWCF          | ●             | -                             | -                | -                     | ●                                         | -                                 |
| GAD-7                                                                                                                                                                                                                                                                                                                                                                                                         | Prospect | PWCF          | ●             | -                             | -                | -                     | ●                                         | -                                 |
| MAD-3 (Medication Adherence Data-3 items)                                                                                                                                                                                                                                                                                                                                                                     | Prospect | PWCF          | ●             | -                             | -                | -                     | ●                                         | -                                 |
| COM-BMQ                                                                                                                                                                                                                                                                                                                                                                                                       | Prospect | PWCF          | ●             | -                             | -                | -                     | ●                                         | -                                 |
| Objective adherence                                                                                                                                                                                                                                                                                                                                                                                           | CFHH     | CFHH          | ●             | -                             | ●                | -                     | ●                                         | -                                 |
| Subjective adherence single question                                                                                                                                                                                                                                                                                                                                                                          | Prospect | PWCF          | ●             | -                             | ●                | -                     | ●                                         | ●                                 |
| Concomitant medications                                                                                                                                                                                                                                                                                                                                                                                       | Prospect | Site          | ●             | -                             | -                | -                     | ●                                         | -                                 |
| Other SAEs                                                                                                                                                                                                                                                                                                                                                                                                    | Prospect | Site          | -             | -                             | ●                | -                     | ●                                         | -                                 |
| Resource use                                                                                                                                                                                                                                                                                                                                                                                                  | Prospect | Site          | -             | -                             | -                | -                     | ●                                         | -                                 |

+ Pseudomonas (or other microorganism) status will be checked together with the monthly prescription

\* Only required where PWCF indicates they have received parenteral antibiotics

\*\* EQ5D-5L collected at the start and end of every exacerbation episode

